#### 11c. Cost outcomes analysis

At the relevant endpoints (10 months after study enrollment for Track 1, delivery for Track 2, and other dates of data censoring), all resource usage and outcome indicators will be extracted from subjects' medical records and case report forms. Unit costs will be obtained from external suppliers and the site's finance and procurement records and applied to the resource usage data to provide a cost per study patient. Costs will be measured from the provider perspective and will include the cost of all resources utilized for each study subject, including drugs, laboratory tests, outpatient visits, and fixed costs such as building space, equipment, and management staff. We will estimate the average cost to the provider per patient achieving viral suppression by 10 months (Track 1) or adhering to ART until delivery as indicated by monthly medication pickup (Track 2). We will also estimate the average cost per other outcomes achieved, such as per patient remaining in care by specified endpoints. The average cost per outcome will then be compared between rapid and standard initiation groups to provide an estimate of the cost-effectiveness of the two strategies. Costs will be reported as means (standard deviations) and medians (IQRs) in rand and dollars.

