## **1. Summary**

One of the most serious challenges facing antiretroviral therapy (ART) programs for HIV/AIDS in resource-constrained settings is the failure of ART-eligible patients to complete the steps required to initiate treatment. The high rate of loss to care of patients who are treatment-eligible at HIV diagnosis may be due in part to the large number of steps required between receiving an HIV diagnosis and obtaining the first dose of antiretrovirals (ARVs). In South Africa, these steps usually require approximately four clinic visits over a period of 2-8 weeks before a patient can start treatment. One strategy proposed for reducing losses among those eligible for ART is to simplify and condense the steps required for starting treatment. This is now possible because new, point-of-care (POC) tests for CD4 counts and TB diagnosis are available. These technologies can be combined with changes to clinic schedules to allow all steps required for ART initiation under South African guidelines (lab tests, physical exam, education) to take place on the day the patient presents for an HIV test.

This study is a randomized strategy evaluation of the feasibility, effectiveness, and cost-effectiveness of rapid ART initiation. Outpatient, non-pregnant, HIV-positive adults who come to a South African clinic for an HIV test, consent to study participation, and are eligible for ART will be randomized 1:1 to rapid ART initiation or to standard care. Those who are assigned to rapid ART initiation will have the possibility of receiving their first dose of ARVs as early as the same day, while those who are assigned to standard care will follow the clinic's usual procedures for starting ART. Rapid ART initiation for HIV-positive pregnant women, which has recently become the standard of care in South Africa, will also be assessed in a programmatic evaluation conducted alongside the randomized evaluation, with a retrospective comparison group. The primary study outcome for non-pregnant adults will be remaining alive, in care and virally suppressed 10 months after having a positive HIV test or CD4 count at the study site. The primary study outcome for pregnant women will be adherence to ART until delivery. The cost effectiveness of the rapid initiation strategy will be assessed as the cost per patient achieving the primary outcome for each population.

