##### 4b. Secondary objectives

1. For non-pregnant adults, compare the cost per patient alive, in care, and virally suppressed within 10 months of an HIV test or enrollment in HIV care for those offered rapid ART initiation to the cost for those offered standard care.
2. For pregnant women, estimate the cost per patient adhering to ART through delivery and the cost per infant infection avoided, using estimated vertical transmission rates.
3. Estimate the proportion of patients alive, on ART, and virally suppressed at 6 month intervals after treatment initiation and at the final date of data censoring.
4. Estimate the average time interval between HIV test or first HIV or ANC care visit and treatment or PMTCT initiation before and after rapid ART initiation became the guideline procedure for pregnant women.
5. If enrollment numbers allow, among pregnant women, stratify the primary outcome (the proportions of subjects achieving retention on ART or PMTCT regimen until delivery) by CD4 count > 350 and  $\leq 350$ .
6. Compare the average gestational age at ART initiation and average number of weeks on ART prior to delivery for pregnant women before and after rapid ART initiation became available.
7. Identify patient-level predictors of treatment uptake, retention in care, and viral suppression.
8. Describe the prevalence of TB symptoms and confirmed TB, time to initiation of TB treatment, and time to initiation of ART among patients with TB.
9. Evaluate the feasibility of the rapid initiation strategy in terms of patient acceptance, actual time between HIV test/enrollment in care and dispensing of first dose of ARVs, and patient costs incurred.

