In Track 1, those in the rapid initiation group will be offered a rapid CD4 count, rapid TB test if needed, and other rapid tests and same-day physical exam, counseling, and adherence education on the same day as study enrollment, allowing immediate ART initiation if eligible. Those in the standard group will follow the standard-of-care visit schedule and procedures, which also include a CD4 count, TB test if needed, other tests, physical exam, counseling, and adherence education, though not on a rapid schedule. Subjects in Track 1 will be prospectively followed for a minimum of 10 months. Follow-up (after treatment initiation) will be passive and by medical record review only, to prevent biasing outcomes through active follow-up and maximize the extent to which study results reflect what could be expected in a routine implementation setting. An additional retrospective comparison group for Track 1 will be enrolled comprised of patients who became eligible for ART at one of the two study sites prior to the launch of the study.

Track 2 will be an observational evaluation only. Data from before the guideline change will be collected retrospectively, from existing registers and records at the site. Data from after the guideline change will be collected prospectively from questionnaires and newly-acrued medical record data. The study will not provide any direct clinical interventions for Track 2.

Unit cost data will be collected for all resources used for patient care for both study tracks, including all drugs, diagnostics, clinical staff time, and infrastructure and other fixed costs. Quantities of resources used will be collected from study case report forms at the end of the follow up period. An average cost per patient and cost per outcome will then be calculated and compared between the strategies.

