## 10. Sample Size

Track 1: In a recent study we conducted in Johannesburg, we found that among patients eligible for ART, 46% initiated ART within 16 weeks of eligibility. In an analysis of data from the same Johannesburg site, we estimated that among more than 3000 patients initiated on ART in 2010 and 2011 who remained in care, 77% were virally suppressed at the routine 6-month viral load. We would thus expect approximately  $0.46 \times 0.77 = 35\%$  of those eligible to have both started treatment and be virally suppressed by the 6-month viral load. For our study site we conservatively estimate that 50% of those eligible for treatment in the standard group will be suppressed by 10 months after their HIV test. We anticipate that the rapid initiation strategy will increase the proportion suppressed to 70%.

For our primary analysis, using an  $\alpha$  of 0.05, power of 90%, 1:1 randomization, and an uncorrected Fisher's exact test, we would need to enroll 124 HIV positive ART-eligible subjects per group (248 total). We expect 70% of all HIV-positive patients to be eligible for ART under current South African guidelines on the day they test positive for HIV or make their first HIV care visit, based on results from published studies in South Africa. Therefore to reach 124 subjects per arm who are treatment eligible on the day of testing we will need to consent 177 subjects per group (354 total). To allow stratification in the analysis by sex and by site, we will consent up to 300 per group (600 total) to have adequate power. We will enroll in the study up to 67% of this total (enrollment=400).

The sample size for the Track 1 retrospective comparison group will be 120. This group will be limited to patients already found to be eligible for ART at one of the two study sites (Thuthukani). They will be compared with each of the two randomized prospective groups (rapid and standard). We expect that Thuthukani will account for approximately 60% of total prospective enrollment of 400, or 120 in each of the randomized prospective groups. We will thus aim to enroll the same the number of subjects into the retrospective comparison group as in each prospective group.

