#### *11a ii. Secondary outcomes*

Secondary outcomes will include:

1. Average cost per patient who is alive, in care, and virally suppressed within 10 months of study enrollment (Track 1).
2. Cost per patient adhering to ART through delivery and the cost per infant infection avoided, using estimated vertical transmission rates (Track 2).
3. Proportion of subjects in each track and group alive, on ART, and virally suppressed at six-month intervals and the final date of data censoring.
4. Average time to ART initiation (days) for each track and group.
5. For Track 2, average gestational age at ART initiation (weeks) and average duration (weeks) on ART prior to delivery.
6. For Track 2, if enrollment numbers allow, proportion of subjects with CD4 count > 350 and ≤ 350 achieving the primary outcome of retention on ART (or PMTCT regimen) until delivery.
7. Patient-level predictors of treatment uptake, retention in care, and viral suppression.
8. Prevalence of TB symptoms and confirmed TB, time to initiation of TB treatment, and time to initiation of ART among patients with TB.
9. Process indicators including:
  - Acceptance of rapid initiation strategy (% of patients offered rapid initiation who accept)
  - Average time elapsed (days) between HIV test and dispensing of first dose of ARVs
  - Average cost to patients of initiating treatment, including travel and other out-of-pocket costs and time spent in clinic

All outcomes will be estimated for each study population and compared between the two study populations where relevant.

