#### 11b. Clinical outcomes analysis

For both tracks and for primary and secondary clinical outcomes, the analytic approach for clinical outcomes will be the same. All analyses will be by intention-to-treat: subjects will be analyzed according to the intervention they were supposed to receive, whether or not they adhere to the defined intervention.

The analysis will begin with a simple comparison of the two treatment groups with respect to baseline predictors of outcomes. We will then conduct a crude analysis comparing the proportion of patients achieving each dichotomous outcome by group and crude risk ratios and 95% confidence intervals

stratified by group. For average gestational age at ART initiation and average time on ART before delivery for Track 2, we will calculate the mean difference between groups and corresponding 95% confidence interval.

Since adherence has been a particular concern for pregnant women who were not eligible for ART under the previous guidelines, the primary outcome for Track 2 will be stratified in secondary analysis by CD4 count at the time of initial ANC visit if enrollment numbers by the end of the study period are large enough to allow a stratified analysis. Subjects in the prospective group found after ART initiation to have CD4 counts above 350 will be compared to those in the retrospective group who were offered AZT under the previous guidelines, while subjects in the prospective group found after ART initiation to have CD4 counts below 350 will be compared to those in the retrospective group who were offered full ART under the previous guidelines.

Because we will not be randomizing large numbers of patients in Track 1 and because no randomization will occur in Track 2, it is possible that some baseline covariates may be imbalanced by treatment arm. To adjust for potential differences by baseline covariates, a log-linear regression model will be used to estimate adjusted risk ratios and a linear regression will be used to adjust mean differences.

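### Track 1 cost-effectiveness is defined by comparing each arm's average cost per success, which does not estimate the added cost per added success

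*Protocol*

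**What the plan says.** The same measure appears in five places in the protocol.

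- Section 1 (Summary): "The cost effectiveness of the rapid initiation strategy will be assessed as the cost per patient achieving the primary outcome for each population".
- Section 4b, first secondary objective, for non-pregnant adults: "compare the cost per patient alive, in care, and virally suppressed within 10 months" between those offered rapid initiation and those offered standard care.
- Section 5a: "An average cost per patient and cost per outcome will then be calculated and compared between the strategies".
- Section 11a ii, first secondary outcome: "Average cost per patient who is alive, in care, and virally suppressed within 10 months of study enrollment (Track 1").
- Section 11c: "The average cost per outcome will then be compared between rapid and standard initiation groups to provide an estimate of the cost-effectiveness".

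For Track 1, no section divides the difference in cost by the difference in outcome. Track 2 also lists a cost per infant infection avoided, but no formula is given and it does not apply to Track 1.

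On precision, section 11c says "Costs will be reported as means (standard deviations) and medians (IQRs) in rand and dollars". It names no interval for a cost difference or for a cost-effectiveness measure. Section 11b, by contrast, specifies "crude risk ratios and 95% confidence intervals" for dichotomous clinical outcomes.

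**The concern.** Section 3c asks whether rapid initiation will be affordable and cost-effective compared with standard care. That is a question about moving from one strategy to the other: what extra is spent, and how many extra patients end up alive, in care and suppressed. An arm's average cost per success answers something else. In the rapid arm it mixes the successes that standard care would also have produced with the extra ones, so the cost of the extra ones cannot be read from it.

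This is a method that the protocol states, not a detail left open. An analysis plan that followed section 11c faithfully would report the averages as the cost-effectiveness result. Two consequences follow. The reported figure can lie well above or well below the cost of an extra success. And a lower average in the rapid arm can be read as a saving when spending per patient has gone up. Section 11e plans to send the findings to national and provincial health departments and to donors, who would be the ones reading the figure.

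**Working it through.** **Inputs from the protocol (section 10).** Success in the standard arm is 0.50 ("we conservatively estimate that 50% of those eligible for treatment in the standard group will be suppressed by 10 months") and in the rapid arm 0.70. Planned Track 1 randomized enrolment is 400, so about 200 per arm.

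**Reproducing the plan's own figure.** Two proportions of 0.50 and 0.70, alpha 0.05 two-sided, power 90%, no continuity correction: 124 per group, as stated. With a continuity correction it is 134. The success rates are therefore read as the plan uses them. The protocol gives no cost figure to reproduce.

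**Assumed inputs.** Standard cost is indexed at 100 per patient. Rapid cost is varied from 110 to 150.

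**Formulas.** Write C for mean cost per patient and p for success proportion, with subscripts S (standard) and R (rapid).

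- Average cost per success in an arm: C / p. For standard, 100 / 0.50 = 200 throughout.
- Added cost per added success: (C_R − C_S) / (p_R − p_S), with p_R − p_S = 0.20.

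| Rapid cost per patient | Rapid average, C_R / 0.70 | Standard average | Added cost per added success, (C_R − 100) / 0.20 |
|---|---|---|---|
| 110 | 157 | 200 | 50 |
| 120 | 171 | 200 | 100 |
| 130 | 186 | 200 | 150 |
| 140 | 200 | 200 | 200 |
| 150 | 214 | 200 | 250 |

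**Where the two measures cross.** Setting C_R / 0.70 = (C_R − 100) / 0.20 gives 0.20 C_R = 0.70 C_R − 70, so C_R = 140. In general the crossing is at p_R / p_S times the standard cost, here 0.70 / 0.50 = 1.4. Below it the rapid average overstates the cost of an extra success (171 against 100 at a cost of 120). Above it the average understates it (214 against 250 at 150).

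**Why.** The rapid average is a weighted mean of standard's average and the added cost per added success, with weights 0.50 / 0.70 and 0.20 / 0.70. At a rapid cost of 130: (0.50 × 200 + 0.20 × 150) / 0.70 = 130 / 0.70 = 186. Most of the weight is on successes that standard care would have delivered.

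**The apparent saving.** At 130 the comparison in section 11c reads 186 against 200, so rapid looks 7% cheaper per success (14 / 200). Spending per patient is 30% higher, and each extra success costs 150.

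**Ranking.** With p_R > p_S, C_R / p_R < C_S / p_S is the same statement as C_R < C_S × p_R / p_S. Subtracting C_S from both sides gives C_R − C_S < C_S × (p_R − p_S) / p_S, that is (C_R − C_S) / (p_R − p_S) < C_S / p_S. So rapid has the lower average exactly when its added cost per added success is below standard's average. Against that benchmark the two measures agree.

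**Precision (secondary).** Simulation with 200,000 draws, 200 per arm, rapid cost 120, normal mean costs and binomial successes, cost and outcome independent within patient. The 95% interval around an added cost per added success of 100 is about 58 to 201, 42 to 216, or 13 to 244 for an assumed cost coefficient of variation of 0.3, 0.5 or 0.8. At 0.5, the difference in averages (171 − 200 = −29) has an interval of about −68 to 7. With an assumed within-patient cost-outcome correlation of 0.6 in each arm it becomes about −57 to −4. Whether the apparent saving is established depends on that correlation, which means, SDs and proportions do not reveal.

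**The case against.** Four points can be made for the plan.

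- **Higher spending is not concealed.** Section 5a plans a comparison of average cost per patient, and section 11b compares the success proportions. Both terms of the incremental ratio are planned outputs, and a reader can divide one by the other. This stands for the point estimate. It does not stand for the interval, which needs patient-level data. Nor does it change which figure the protocol names as the cost-effectiveness result.
- **The two measures rank the arms alike.** This stands, as shown in the working, and it limits the harm. At planning rates, with rapid below 1.4 times the standard cost, the average errs against rapid by overstating the cost of an extra success.
- **No threshold is in play.** A reader might infer that following the plan would make rapid initiation pass a willingness-to-pay limit that it should fail. The documents do not support that. They state no threshold and no affordability rule, and section 11c compares the two arms with each other. Take assumed costs of 200 and 350 per patient: the averages are 200 / 0.50 = 400 and 350 / 0.70 = 500, and an extra success costs 150 / 0.20 = 750. A conflict appears only if an outside limit between 500 and 750 is applied to the rapid arm alone. The plan's own comparison, 500 against 400, already shows rapid as the dearer way to a success.
- **Intervals belong in an analysis plan.** This largely stands. The interval method and any acceptability curve can properly be left there, so their absence is not an error in the protocol. Section 11c costs each study patient, so nothing planned prevents an interval.

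**Conclusion.** The concern holds in a limited form. The Summary and section 11c fix a measure that does not estimate the added cost per added success, although section 3c asks the comparative question. At the protocol's 50% and 70%, the rapid average is too high as a guide to the cost of an extra success below 1.4 times the standard cost (171 against 100 at 1.2 times) and too low above it (214 against 250 at 1.5 times). Between 1 and 1.4 times, it reads as a saving per success while spending per patient rises.

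These sizes rest on assumed cost levels, because the protocol gives none. The 1.4 follows from the planned success rates alone and will move with the observed ones. The intervals rest further on assumed cost variability and, except where stated, on independence of cost and outcome.

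This is a minor improvement to a secondary objective. The primary clinical result is not affected, and the documents do not support the reading that the plan reverses the ranking of the strategies.

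**What to change.** In section 11c, and in the matching sentence of the Summary, make the main Track 1 cost-effectiveness measure the difference in mean cost per enrolled subject divided by the difference in the proportion achieving the primary outcome, by randomized group. Report the two differences alongside the ratio, so that a case where rapid is both cheaper and better, or where the difference in success is close to zero, can be read correctly. Keep each arm's average cost per success as a descriptive figure.

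As a secondary step, give the measure a 95% interval by resampling patients within arm, keeping each patient's cost and outcome together so that their correlation is preserved. The details, and an acceptability curve if wanted, can go in the analysis plan.

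The cost is a few sentences of wording and a little analysis work. Section 11c already yields a cost per study patient alongside outcomes, so no new data are needed.

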#### 11d. Analysis of process indicators

In order to help inform treatment providers and policy makers of the implications of rapid ART initiation in terms of patient acceptance, impact on staff, laboratory work flow, and other patient-level and health systems factors, we will generate descriptive statistics for process indicators for both initiation strategies, including:

- Acceptance of rapid initiation strategy (% of patients offered rapid initiation who accept and frequency of reasons for refusals where provided)
- Mean time elapsed (days) between HIV test and dispensing of first dose of ARVs
- Mean time (hours: minutes) spent in clinic by patients receiving rapid and standard initiation, based on recorded start and end time for each clinic visit.
- Mean cost (rand) to patients of making the clinic visits required for treatment initiation, including transport fares, lost wages, and other costs reported in the baseline questionnaires.

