#### **5. Study Design**

##### 5a. Overview of study design

The study will be divided into two tracks, based on the study populations to be included.

Track 1: *Non-pregnant adults*. Track 1 will be a randomized comparison of rapid initiation of ART to the current standard of care for non-pregnant, treatment eligible adults. Patients testing positive, providing a blood sample for a CD4 count, or receiving a CD4 count result will be individually randomized 1:1 to either the rapid ART initiation strategy (rapid group) or the standard ART initiation strategy (standard group). Patients in the rapid group who are found to be eligible for ART will be offered the opportunity to initiate ART in the fastest time feasible given individual circumstances, and whenever possible on the same day as study enrollment. Patients in the standard group will be offered standard treatment initiation as currently implemented by the study site.

Track 2: *Pregnant women*. Track 2 will be a programmatic evaluation of rapid initiation of ART for pregnant women. Immediate ART initiation on the day of a woman's first antenatal care visit was introduced in South Africa in a guideline revision in April 2013 and is now the standard of care at the study site. Guidelines call for women to remain on ART for the duration of pregnancy regardless of their initial CD4 count. Adherence to ART during pregnancy, as measured by monthly medication pickups, will be compared to adherence before rapid initiation was offered.

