#### *Inclusion criteria:*

- Adult patients ( $\geq 18$  years)
- For Track 1, tested HIV-positive at study site's outpatient testing service on day of study enrollment or previously tested HIV-positive but providing a blood sample for a CD4 count or receiving CD4 count test result on day of study enrollment
- Eligible for antiretroviral therapy under prevailing South African guidelines\*

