#### *Exclusion criteria:*

- Currently on ART or on ART at any time in the past 12 months (three-drug combination; previous PMTCT regimen exposure for an earlier pregnancy is not an exclusion criterion)
- Stated intention to seek further HIV care during the next 12 months or antenatal care before completion of the current pregnancy at another site, not at the study site
- Not physically or emotionally able to participate in the study, in the opinion of the investigators
- Not willing or able to provide written informed consent to participate in the study

- Previously enrolled in the same study
- Diagnosed with drug-resistant TB or on MDR-TB treatment
- For Track 1 only, pregnant (pregnancy is an exclusion criterion for Track 1 because treatment guidelines for pregnant women differ from those for non-pregnant adults)

*\*Current South African treatment eligibility criteria for non pregnant HIV-positive adults are:*

- *CD4 count  $\leq$  350; or*
- *Tuberculosis, regardless of CD4 count; or*
- *WHO Stage 4 or Stage 3 condition, regardless of CD count (hereafter “Stage 4/3”)*

*All pregnant HIV-positive women are eligible for ART.*

Subjects in Track 1 will be followed prospectively and will be asked for written informed consent prior to study enrollment. An additional Track 1 retrospective comparison group will be enrolled comprised of patients who became eligible for ART at one of the two study sites (Thuthukani Clinic) prior to the launch of the study, with data collection limited to retrospective medical record review. In Track 2, subjects offered rapid initiation by the study clinic under the new standard of care will be followed prospectively and asked for written informed consent before study enrollment. For subjects in the comparison group in Track 2, data will be collected retrospectively through medical record review only. The study team will have no contact with these subjects, and informed consent will not be sought.

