#### 8e. Medical record data

Most data for the study will be collected from the site's routinely maintained electronic medical records, which are maintained in an information system called Therapy Edge-HIV™. Records in this information system are typically only created once a patient starts ART. Paper-based medical records kept by the site will therefore be used to supplement the electronic medical record system as needed. The fields to be collected are listed below.

*To be used to link electronic and paper-based records to study identification number only:*

- Electronic medical record system number
- Clinic file numbers
- National ID number
- Name
- Date of birth

*All subjects at baseline (ART initiation):*

- Date of positive HIV test (if available)
- Sex
- Age in years
- Weight and height or BMI
- Date treatment eligibility determined, if reported
- Date and result of eligibility-determining CD4 count
- Date and result of TB symptom screen
- Date, type, and result of TB test(s)
- TB treatment, if relevant
- WHO stage and clinical conditions
- Date ART initiated (first dose of drugs dispensed)
- First-line regimen prescribed

*For all clinic visits for duration of study follow up, including initial visit and pre-ART visits (to be used to estimate resource utilization):*

- Date of visit
- Primary reason for visit (e.g. scheduled medical visit, medication pickup, unscheduled medical visit)
- Types of professionals seen (e.g. nurse, doctor, pharmacy assistant, counselor)
- Group and individual sessions attended (e.g. wellness course, adherence education)
- Numbers and types of all lab tests conducted (including CD4 counts and viral loads)
- Other procedures (e.g. x-rays) performed

- Medications prescribed and dispensed (ARV and non-ARV)
- Admissions for inpatient care since previous visit, if recorded
- Details of inpatient care received (facility, number of days, medications, lab tests, etc.) if recorded

*At interim and final dates of data censoring:*

- Date and result of most recent viral load test
- Status at clinic (in care / died / transferred to another site / stopped care / lost to follow up, defined as > 1 month late for last medication pickup)
- New or recurring HIV-related conditions
- Date and cause of death if applicable
- Date and result of most recent CD4 count

*Track 2 subjects only (pregnant women):*

- Gestational age at diagnosis or first ANC visit for current pregnancy if previously diagnosed
- Prior exposure to PMTCT

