## 11. Outcomes and Data Analysis

### 11a. Outcomes

#### 11a i. Primary outcome

Track 1: The primary outcome for Track 1 is the proportion of subjects in each group alive, in care and virally suppressed at the routine six-month on ART monitoring visit within 10 months of a positive HIV test or initial HIV care visit if previously diagnosed. The analysis period will start at study enrollment and continue through the earlier of the patient's six-month viral load or 10 months after the patient's HIV test.

Under South African treatment guidelines, all ART patients have a monitoring viral load done at six months after ART initiation. We will use this measure to assess our primary outcome. In order to create comparable follow-up time in both groups and to allow all subjects enough follow up time to have a six-month viral load, for the primary outcome analysis we will consider all ART-eligible patients who do not have a six-month viral load for any reason within 10 months of study enrollment to be failures. Viral suppression will be defined as <50 copies/ml. Patients in the rapid group who do not initiate treatment on the day of their HIV test will remain in the intervention arm for analysis (i.e. intention to treat).

Our primary outcome will be measured 10 months after study enrollment because the first 6 months on ART is the time when patients are most likely to be lost or die. At the 10-month point after study enrolment, all subjects who started ART within 3 months of enrolment will have had the opportunity for at least 6 months of exposure to treatment and allow an additional month for subjects to return to the clinic for their routine 6-month viral load test. If rapid initiation triggers a higher rate of loss to follow up after starting treatment, the impact is likely to be evident within six months of initiation. Six months of ART is also sufficient to achieve viral suppression in the vast majority of patients. In an analysis of >13,000 patients who initiated ART at a large clinic in Johannesburg, 75-80% of all patients were virally suppressed after a median (IQR) of 3.9 (3.7-5.0) months. We would thus expect at least 80% of patients to reach viral suppression by 6 months on ART.

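### The time-to-first-ARV process indicator starts at the HIV test and omits the alternative start that objective 9 and the primary outcome give for previously diagnosed patients

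*Protocol*

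**What the plan says.** The indicator appears twice in the protocol, each time with the HIV test as its only starting point:

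- Section 11d: "Mean time elapsed (days) between HIV test and dispensing of first dose of ARVs".
- Section 11a ii, item 9: "Average time elapsed (days) between HIV test and dispensing of first dose of ARVs".

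The Track 1 inclusion criteria (section 5c) admit, besides those testing positive on the day, patients who "previously tested HIV-positive but providing a blood sample for a CD4 count or receiving CD4 count test result on day of study enrollment". Nothing in the criteria limits how long ago the diagnosis was made. The nearest exclusion, "Currently on ART or on ART at any time in the past 12 months", concerns past treatment only.

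Elsewhere the protocol allows for this group:

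- Section 4b, objective 9, which the indicator serves: "actual time between HIV test/enrollment in care and dispensing of first dose of ARVs".
- Section 11a i, primary outcome: "within 10 months of a positive HIV test or initial HIV care visit if previously diagnosed".

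Section 5a times a rapid start against the study visit: "whenever possible on the same day as study enrollment". Section 8e lists the date of the positive test as an item to be collected only where it can be found.

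**The concern.** The indicator is meant to tell providers and policy makers how quickly treatment starts under each strategy. For a patient diagnosed well before the study visit, the interval from test to first dose has two parts: the time from diagnosis to the visit, which the strategy cannot influence, and the time from the visit to dispensing, which it can. Following 11d as written adds the two together. A same-day start, the result the strategy aims for, would then be recorded as a delay of months or years if the diagnosis was that old. A patient whose test date cannot be found would have no value at all. Because the summary is a mean, a minority of long gaps can move it noticeably.

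This is separate from the handling of patients who never start. It affects patients who do start.

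**Working it through.** The protocol states no expected value for this indicator, so there is no figure to reproduce. The check has three steps.

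**1. Individual scores**

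| Rapid-group patient, dispensed on the study day | From HIV test (11a ii, 11d) | From study-day visit |
|---|---|---|
| Tested positive that day | 0 days | 0 days |
| Tested 365 days earlier, CD4 draw that day | 365 days | 0 days |
| Tested 18 months earlier (1.5 × 365.25) | about 548 days | 0 days |
| Tested earlier, date not found | no value | 0 days |

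**2. Shift in an arm's mean**

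Let f be the share previously diagnosed and m their mean days from HIV test to study visit. The rise in the mean is f × m. The protocol gives neither input, so both are assumptions:

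- f = 10%, m = 30: 3 days
- f = 10%, m = 180: 18 days
- f = 25%, m = 180: 45 days
- f = 25%, m = 365: about 91 days
- f = 50%, m = 365: 182.5 days
- f = 50%, m = 730: 365 days

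If every rapid patient started on the study day, these would be the reported means instead of 0. The direction is certain and the size is not known.

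**3. Effect on the comparison between arms**

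Randomization should give both arms the same f and m on average, so f × m cancels from the expected difference. What remains is extra variance. If the gap is exponential with mean m (a further assumption), the added between-patient SD is m × √[f(2 − f)]. With 200 per arm (400 enrolled, section 10), all starting, the added standard error of the difference is SD × √(2/200) = SD × 0.10.

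| f, m | Added SD | Added SE of the difference |
|---|---|---|
| 20%, 90 days | 90 × √0.36 = 54 days | about 5 days |
| 30%, 180 days | 180 × √0.51 = 129 days | about 13 days |
| 50%, 365 days | 365 × √0.75 = 316 days | about 32 days |

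If only 140 per arm started (assumed), the multiplier is √(2/140) = 0.12 and the three values become about 6, 15 and 38 days. In the middle case with 200 per arm, the added component alone is worth roughly ±1.96 × 12.9 = ±25 days at 95%.

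**The case against.** The strongest reply is that the HIV test is shorthand here. Section 11a i gives the full form for the primary outcome and then, for the same mixed population, refers simply to ten months after the HIV test. A test from 18 months earlier cannot be what is meant there, so the two bullets may just have dropped half a phrase. That is plausible, and a wording slip is the likeliest explanation. But nothing in item 9 of 11a ii or in 11d restores the missing half, and an analyst following either would compute the wrong interval.

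It can also be said that item 4 of 11a ii already covers average time to ART initiation. That item states no starting point, so it does not repair item 9.

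That the indicator is descriptive and feeds neither the primary outcome nor the sample size is correct, and it limits the weight of the point.

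A reader might infer more than the documents support:

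- *That the added noise swamps the delay under study.* This would set a between-patient SD (129 days in the middle case) against a mean delay. For comparing arm means the standard error matters, and there it is about 13 days.
- *That the 42-day interval in section 3b is the yardstick.* That figure runs from the first CD4 count showing eligibility, among those who started within 16 weeks. It has a different origin and a selected group.
- *That the indicator would mostly reflect time since diagnosis.* This depends on f and m, which the protocol does not give; at 10% and 30 days the rise is only 3 days.

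**Conclusion.** The point holds as an inconsistency between a stated derivation and its own objective. As written, item 9 of 11a ii and 11d give a previously diagnosed same-day starter the days since diagnosis instead of 0. This inflates the absolute mean in each arm and adds noise to the comparison. The size cannot be computed from the documents; under the assumed shares of 10–50% and mean gaps of 30–730 days, the rise runs from 3 to 365 days.

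It would be wrong to conclude that the comparison between rapid and standard initiation is biased. The expected difference is largely preserved by randomization. The reported level in each arm, which is what a descriptive feasibility figure conveys, is what goes wrong. This is a modest point, worth correcting because the correction is so small.

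**What to change.** In section 11a ii, item 9, and section 11d, bring the starting point into line with objective 9 by measuring from the qualifying study-day visit (HIV test, CD4 draw or CD4 result) to first dispensing. In the two randomized arms, use the date of consent/randomization for that visit. It falls at the same point in both arms, whereas sections 6b vi and 8f ii confirm a standard-group patient's enrollment only once eligibility is known. Report time since HIV diagnosis separately as a baseline characteristic, where the date is known.

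The cost is one line of wording in each place, with no new visit or data item. The dispensing date comes from the CRF for the rapid group and from medical records for the standard group: section 8c stops CRF entry for standard subjects once eligibility is recorded, so the CRF alone is not enough. The primary outcome definition and the sample size stay as they are.
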